**Methods:**

A baseline and a longitudinal questionnaire in the Lucy app collects real-world, self-reported information on symptoms of endometriosis, socio-demographics, mental and physical health, economic factors, nutritional, and other lifestyle factors. 5,000 women with confirmed endometriosis and 5,000 women without diagnosed endometriosis in a control group will be enrolled and followed up for one year. With this information, any connections between recorded symptoms and endometriosis will be analyzed using machine learning.

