## Introduction

Endometriosis is a chronic inflammatory disease with endometrium-like tissue outside the uterine cavity [1, 2]. It is commonly associated with chronic pelvic pain, infertility, and decreased quality of life, although asymptomatic cases exist [3–5]. The exact prevalence of endometriosis is unknown, but it may affect 5–10% of women and those assigned female at birth during their reproductive years, which equals nearly 190 million people worldwide [1]. Despite this high prevalence, recognition of the disease is inadequate, underprioritized, and research is underfunded, contributing to diagnostic delays ranging from 4 to 11 years [6–9]. Accordingly, endometriosis should be considered a public health issue, and reducing the current diagnostic delay is paramount.

Lucy is a mobile health application (Lucy app) designed to alert users with an increased risk of endometriosis to seek medical attention. Users can input their menstrual cycle information, health status, medical records or diagnoses, dietary details, lifestyle, and pain symptoms. Specialists in reproductive gynecology and health psychologists developed the app’s algorithm to continuously analyze the recorded data and alert the user when the entered symptoms are strongly associated with endometriosis.

A baseline questionnaire and a longitudinal questionnaire were developed and implemented as an additional module in the Lucy app. It collects self-reported data on symptoms of endometriosis, socio-demographics, mental and physical health, economic factors, nutrition, and other lifestyle factors [10]. By linking the collected information with existing registry-based information on diagnoses of endometriosis, healthcare use, and the big data approach, we can develop a phenotype description of individuals with endometriosis and structured clinical data [11].

So far, only one study has investigated this question with big data analysis using machine learning (ML). According to Bendifallah *et al*., endometriosis can generally be diagnosed with high diagnostic accuracy based on endometriosis-related symptoms and demographic data using ML technology [12]. The work presented by these authors was based on medical records of 800 participants of a French cohort and not on patient self-reported data.

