### Who would benefit from the early diagnosis of the disease?

In patients with negative imaging, the definitive diagnosis of endometriosis is still laparoscopic intervention and histological analysis, which requires invasive evaluation and direct visualization of lesions, followed by histological analysis [6]. To initiate treatment, including surgery, we need a clinical hypothesis based on signs and symptoms of endometriosis, which can lead to a late diagnosis of the disease. Due to the lack of non-invasive diagnostic tools, the average delay in diagnosing endometriosis from the onset of the symptoms is 11.7 years in the United States, 8 years in the United Kingdom, and 3.9 years in Hungary [14, 15]. A non-invasive diagnostic tool would be crucial in early endometriosis diagnosis, especially the minimal-mild (#Enzian P, ASRM Stage I-II) endometriosis [16, 17].

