## Objectives

### Primary objective

To establish a comprehensive real-world big data repository using the *Lucy app*. This initiative aims to identify unique clinical cohorts by leveraging various factors such as digital footprints, symptoms, patient experience, comorbidities, clinical severity, and lifestyle patterns. Using ML for big data analytics, patient profiles and structured clinical data that facilitate the earlier detection of endometriosis can be generated. Ultimately, this approach has the potential to reduce the current diagnostic delay associated with endometriosis significantly.

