### Eligibility criteria

5,000 women with confirmed endometriosis and 5,000 women without diagnosed endometriosis in a control group aged 18–45 years will be enrolled and followed up for one year.

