### Questionnaire

Participants will be asked to complete a baseline questionnaire once and a longitudinal questionnaire monthly for one year. The questionnaire includes questions about endometriosis symptoms, socio-demographic information, mental and physical health, known medical conditions, medication use, dietary habits, economic burden, and lifestyle factors. These include free-text responses, single or multiple-choice questions, and numerical rating scales. See Supplementary Data for the questionnaires and https://hellolucy.app/en/ for the Lucy app.

Self-reported data of the participants will be measured as follows:

Evaluating the quality of life using the 5-level EQ-5D (EQ-5D-5L) and Endometriosis Health Profile 5 (EHP-5) [18].Assessing pain scores using the Visual Analogue Scale (VAS) [19].Examining somatic and emotional symptoms associated with central pain sensitization using the short version of the Central Sensitization Inventory (CSI-9) [20].

If using the same user account, Lucy app users can pause and resume completing the questionnaire, even on different devices. Once all questions have been answered, users can review and modify their answers on a summary screen. When they submit the questionnaire, their responses are stored on a server. At this point, the questionnaire’s content is fixed and cannot be changed.

In longitudinal studies, minimizing the drop-out rate and encouraging maximum user participation in completing the desired quantity of questionnaires is crucial. *Lucy app* users are anonymous; therefore, personal email contact is impossible. To address this challenge and reduce dropouts, the application uses several methods to notify users when the questionnaire becomes available for completion again. The questionnaire menu is prominently displayed on the application’s main page, and a pop-up window alerts users that the questionnaire is complete. Users can track the number of times and when they completed the questionnaire, but detailed completion data is not visible. The app displays a pop-up window with motivational quotes and positive messages to encourage and support users. In addition, users who complete the questionnaire are entered into a drawing as an additional incentive to participate. These measures are designed to minimize dropout and maximize user engagement in completing the questionnaires for the study.

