### Statistical and machine learning analyses

Our dataset comprises both diagnosed and undiagnosed patients, enabling us to evaluate the quality of the data. The goal is to have a case-control ratio of 1:1 in the dataset. Specifically, records from patients diagnosed with endometriosis but not yet received treatment should highly correlate with well-known endometriosis-associated symptoms, such as pelvic pain.

The normal distribution of the data will be tested with histograms and QQ-plots. Continuous variables will be presented as averages (mean ± SD), nominal variables as numbers (n) and percentages (%). A level of statistical significance of P < 0.05 will be used. The VAS scores of the endometriosis group and the reference group will be compared with independent sample t-tests. Also, independent samples t-tests will be conducted to see whether EQ-5D-5L, CSI-9 and EHP-5 scores were different between diet-users and non-diet users. Subsequently, a one-way analysis of variance of no diet use and the various diets will be carried out for the EQ-5D-5L, CSI-9, and EHP-5 scores. A post-hoc multiple comparisons analysis (Tukey honestly significant difference) will be used to identify where the differences between these diet groups were located. Preliminary analyses will involve various correlation techniques and visual representations, including heat maps contrasting diseases against symptoms.

To explore associations between diseases, symptoms, severity, dietary habits, and lifestyle activities, we will employ Cramér’s V statistical method. Additional validation of patient segmentation will be conducted to confirm that emerging patient cohorts exhibit anticipated symptoms. Machine learning algorithms will be deployed to uncover hidden relationships or patterns. Density-Based Spatial Clustering of Applications with Noise (DBSCAN) and Uniform Manifold Approximation and Projection (UMAP) will be employed to visualize high-dimensional symptom and activity spaces in 2D or 3D representations for dimensionality reduction and clustering. Risk assessments for undiagnosed patients will be computed using Random Forest and Long Short-Term Memory (LSTM) models. The LSTM models will fully leverage the time-series data, offering predictive insights into disease outcomes based on the temporal progression of symptoms.

All the methodologies above will be tested under various scenarios, such as:

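### As written, the LSTM and Random Forest can show discrimination of diagnosed endometriosis but not earlier detection, because the cases' study questionnaires contain no time before diagnosis

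*Protocol article*

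**What the plan says.** The eligibility section sets the two groups: "5,000 women with confirmed endometriosis and 5,000 women without diagnosed endometriosis in a control group aged 18–45 years will be enrolled". Both are "will be enrolled and followed up for one year". Under Questionnaire, participants are to "complete a baseline questionnaire once and a longitudinal questionnaire monthly for one year".

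The primary objective is that "patient profiles and structured clinical data that facilitate the earlier detection of endometriosis can be generated". The interval to be shortened appears twice: the Introduction describes poor recognition of the disease as "contributing to diagnostic delays ranging from 4 to 11 years", and the section on who would benefit gives national averages from symptom onset of "11.7 years in the United States, 8 years in the United Kingdom, and 3.9 years in Hungary".

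Statistical and machine learning analyses assigns risk assessment of undiagnosed women to Random Forest and LSTM models, and says of the latter: "The LSTM models will fully leverage the time-series data, offering predictive insights into disease outcomes based on the temporal progression of symptoms". The scenarios listed at the end of that section are all variables, a reduced variable set, and analyses split by diagnosis status.

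**The concern.** A model meant to flag women sooner has to be judged on data from before they were diagnosed. Here the positive class consists of women whose diagnosis was already made when their study questionnaires began. Their symptom course may reflect years of known disease, treatment or surgery. The fitted models would then score women at a different stage, those with no diagnosis.

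Good separation of the two groups would be a legitimate result, but it would not show that any woman is flagged earlier than she would otherwise have been diagnosed. None of the three listed scenarios tests timing. They check whether results are consistent across variable sets and diagnosis strata. The risk is that a discrimination result is reported as support for the primary objective.

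This is not a detail that an analysis plan can supply later. Enrolment status and length of follow-up are fixed in this document, and no later plan can create pre-diagnosis follow-up in women already diagnosed at entry.

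**Working it through.** The article has no derived figure to reproduce on this point. The 5,000 + 5,000 enrolment agrees with its stated 1:1 ratio.

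**Inputs from the article:** 5,000 prevalent cases and 5,000 controls (Eligibility criteria); one year of follow-up with one baseline and monthly questionnaires (Questionnaire); delay D of 3.9 to 11.7 years (Who would benefit); population prevalence of 5-10% (Introduction).

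**Assumptions:** the share u of controls with undiagnosed disease equals the 5-10% prevalence, with 30% as a sensitivity value; the diagnosis rate is constant at 1/D per year; there is no drop-out.

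**Step 1. Pre-diagnosis time in cases' study questionnaires.** Diagnosis precedes enrolment and enrolment precedes every questionnaire, so the prospective pre-diagnosis time is 0 months for all 5,000.

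**Step 2. Follow-up against the delay.** 1/3.9 = 25.6% and 1/11.7 = 8.5%. A control followed for the full year therefore shows at most about a quarter of the shortest stated average delay.

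**Step 3. Controls newly diagnosed during the year.** Expected number = 5,000 × u × (1 − exp(−1/D)). The one-year probability is 1 − exp(−1/3.9) = 0.2262, or 1 − exp(−1/11.7) = 0.0819.

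| u | Undiagnosed controls | D = 11.7 years | D = 3.9 years |
|---|---|---|---|
| 5% | 250 | 20 | 57 |
| 10% | 500 | 41 | 113 |
| 30% | 1,500 | 123 | 339 |

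For u of 5-10% the range is 20 to 113 women, or 0.4% to 2.3% of the 5,000 controls. Multiplying by the rate itself would give 5,000 × 0.10 / 3.9 = 128 at the top, but that treats a rate as a probability.

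**Step 4. Lead available in those women.** It is at most 12 months. With h = 1/D, the mean time from enrolment to diagnosis among those diagnosed within the year is 1/h − exp(−h)/(1 − exp(−h)). This is 5.8 months at D = 4 and 5.9 months at D = 11.

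**Step 5. Other records.** The study questionnaires number at most 10,000 × 13 = 130,000. The article refers to a dataset of over a million patient records, which would be 1,000,000 / 10,000 = 100 per enrolled woman. Other app records therefore appear to be meant. Their timing relative to diagnosis is not stated, nor is whether they feed the LSTM.

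**The case against.** The strongest counter-argument is that the LSTM's input is described only as time-series data. The Introduction describes app entries outside the study module, the data-quality section filters activity records, and the record count far exceeds the possible questionnaires. A reader might infer from the design that the model never sees pre-diagnosis data and that the study cannot show earlier detection. The documents do not support that reading, because some app records could predate diagnosis and the text does not say either way. What stands is narrower: the cases' study questionnaires contain no such time, and no other source is named as model input. Registry linkage is mentioned as an aim, but not as LSTM input, and it is hard to reconcile with anonymous users and no stored identifiers.

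A reader might also infer that the cases' follow-up is the first year after diagnosis. It is not so defined. Cases may have been diagnosed long before entry.

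The benefit wording is hedged (may, could, potential), and the LSTM sentence speaks of disease outcomes, not lead time. The article thus does not promise to demonstrate a shorter delay, and a diagnosed-versus-undiagnosed classifier is a reasonable first step. This limits the point to what may be concluded. It does not remove it, since earlier detection sits in the primary objective.

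Training sets, index dates and performance measures are properly left to a fuller document, and their absence is not the complaint. The article does single out diagnosed but untreated women, but as a data-quality check. It also splits analyses by diagnosis status. Neither supplies lead time.

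Finally, the count in the working is soft. Prevalence in the population is not the undiagnosed share among app users, drop-out is ignored, and the app's own alerts could change the diagnosis rate.

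**Conclusion.** The point holds in this limited form and should be acted on. On the plan as written, results from the prevalent cases can support discrimination of diagnosed disease, and evidence for earlier detection must come from elsewhere. That the case questionnaires contain no pre-diagnosis time follows from the enrolment rule and needs no assumption.

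The size of the prospective alternative does rest on assumptions. It is tens to just over a hundred women at the article's own prevalence and delay figures, and more if undiagnosed disease is commoner among app users. Even at 30% it stays far below 5,000, so the conclusion does not depend on the exact count. The data bank itself remains useful. If dated app records from before diagnosis exist and enter the models, the limitation would be eased to the extent that they do, and the sponsor should say so.

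**What to change.** 1. Keep or add a dated diagnosis item in the monthly form. The article lists known medical conditions among the questionnaire topics but does not confirm a monthly diagnosis item.
2. Treat women newly diagnosed during follow-up as a separate incident-case set, held out of training.
3. Evaluate earlier detection only in that set, and in any app records shown to predate diagnosis. Use only records dated before diagnosis, and report lead time as months from model flag to diagnosis.
4. State which records feed the LSTM and whether any predate diagnosis.
5. Describe results from the prevalent cases as discrimination of diagnosed disease, and draw no conclusion from them about earlier detection or reduced delay.

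The cost is one questionnaire item if it is not already there, some analysis specification, and tighter wording of conclusions. Recruitment need not change. The downside is that the earlier-detection estimate will be imprecise, and in the prospective set its lead time is capped at 12 months.

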### Data quality assessment and preprocessing

Given that real-world data inevitably contain inaccuracies, inconsistencies, text inputs, and non-qualitative information, the initial phase of our analysis is dedicated to data quality assessment and filtering. Various data quality metrics will be used, such as confirming the expected data types for each column. We will exclude records with invalid activity dates, missing activity information, users with implausible ages, and a low frequency of activity records. Statistical evaluations will be performed to assess the general data quality. For instance, the distribution of records across different days of the month should be consistent, without significant drop-offs on specific days such as the 31st. The data quality assessment metrics will understand the validity, integrity, precision, reliability, and timeliness of the data to ensure that the primary and secondary objectives can be met with the collected data. After initial filtering, we’ll dive deeper into removing non-qualitative or irrelevant data. Each symptom will be analyzed in terms of its absolute frequency and temporal distribution. Symptoms with sparse records will be discarded to prevent statistical anomalies. Any symptoms showing unrealistic temporal distributions will be subject to medical review to ensure the data’s authenticity.

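### If form completion differs by diagnosis, an LSTM on series of unequal length could partly learn completion rather than symptoms; the plan fixes no common observation window

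*Protocol article*

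**What the plan says.** All references are to the protocol article, under Materials and methods.

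- **Forms.** The Questionnaire section states: "Participants will be asked to complete a baseline questionnaire once and a longitudinal questionnaire monthly for one year". That is at most 1 + 12 = 13 forms per woman.
- **Drop-out.** The same section says that "minimizing the drop-out rate and encouraging maximum user participation in completing the desired quantity of questionnaires is crucial". Users are anonymous and cannot be e-mailed. The remedies are in-app notices, motivational messages and a prize drawing, none of them described as differing by group. No drop-out rate is given.
- **Filter.** Data quality assessment and preprocessing states: "We will exclude records with invalid activity dates, missing activity information, users with implausible ages, and a low frequency of activity records". No threshold is given.
- **Models.** Statistical and machine learning analyses states: "Risk assessments for undiagnosed patients will be computed using Random Forest and Long Short-Term Memory (LSTM) models". It adds: "The LSTM models will fully leverage the time-series data, offering predictive insights into disease outcomes based on the temporal progression of symptoms".
- **Test scenarios.** Three examples follow: all variables, a reduced set of variables, and a split by diagnosis status. None of them varies the observation window.
- **Aim.** The primary objective is earlier detection of endometriosis.

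**The concern.** A commitment to use the time series in full, combined with expected drop-out, means that the model inputs will differ in length and in their gaps. A sequence model given such series can respond to length and gaps as well as to symptom content. If diagnosed women and controls complete forms at different rates, length is associated with the label, and the model can gain discrimination from it.

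That gain would not carry over to the intended use. A new user, at the moment when early detection is wanted, has no year of completion history. Reported performance on the primary objective could therefore be higher than what the app would achieve in practice.

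The low-frequency exclusion cuts off the shortest series but leaves the rest unequal. The three named scenarios change which variables enter or which women are analysed. Agreement between them would not show whether series length contributes.

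**Working it through.** The article states no AUC, accuracy, drop-out rate or completion by group, so there is no figure of its own to reproduce. What follows is an illustration.

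**Inputs**
- From the article: 1 baseline form plus 12 monthly forms, and a 1:1 ratio of cases to controls.
- Assumed: constant monthly retention r in each group, a symptom score with a true AUC of 0.75, and form count independent of that score within each group.

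**Step 1. Number of forms N.** P(N = k) = r^(k−1)(1 − r) for k = 1 to 12, and P(N = 13) = r^12. For example, r = 0.95 gives 0.95^12 = 0.54 completing everything, and r = 0.85 gives 0.85^12 = 0.14.

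**Step 2. AUC of the count alone.** AUC = Σ P_case(k) × [P_control(N < k) + 0.5 × P_control(N = k)].

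**Step 3. AUC of symptoms and count together.** The symptom score is N(d, 1) in cases and N(0, 1) in controls, with d = √2 × Φ⁻¹(0.75) = 0.954. The best combined score is dX + L(N), with L(k) = ln[P_case(k)/P_control(k)]. Its AUC is ΣΣ P_case(i) P_control(j) Φ[(d² + L(i) − L(j))/(d√2)].

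| Monthly retention, case v control | All 12 months completed | Count-only AUC | Count-only AUC, minimum 6 forms | Apparent AUC (true 0.75) | Inflation |
|---|---|---|---|---|---|
| Equal | equal | 0.500 | 0.500 | 0.750 | 0 |
| 92% v 90% | 37% v 28% | 0.552 | 0.543 | 0.754 | 0.004 |
| 95% v 90% | 54% v 28% | 0.646 | 0.615 | 0.783 | 0.033 |
| 90% v 80% | 28% v 7% | 0.675 | 0.661 | 0.797 | 0.047 |
| 95% v 85% | 54% v 14% | 0.740 | 0.702 | 0.830 | 0.080 |

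**Step 4. Sensitivity**
- Swapping the two groups, so that controls complete more, gives the same apparent AUCs. The direction of the difference does not matter.
- With a true symptom AUC of 0.65, the four unequal rows give apparent AUCs of about 0.66, 0.71, 0.73 and 0.78.
- Setting 12-month completion directly, 60% v 40% gives a count-only AUC of 0.608 and an apparent AUC of about 0.77. 50% v 20% gives 0.679 and about 0.80 (both with true AUC 0.75).
- A minimum-record filter, with thresholds assumed because none is stated, lowers the count-only AUC but does not remove it (fifth line of the table: 0.740 to 0.702 at a minimum of 6 forms).
- If every woman contributes the same number of time points, the count-only AUC is 0.500 in every scenario.

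**The case against.** **The text does not say that unaligned series go in.** A reader might infer that each woman's whole record enters unmodified, or that the form count is a predictor. Neither is stated. The article gives the basis of prediction as "based on the temporal progression of symptoms", which names symptoms and not completion. This stands, and the point is therefore conditional. The stated intention does not by itself take length or gaps out of the input.

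**Windows, padding and masking belong in a fuller plan.** This also stands: an article may leave them out, and their absence is not an error. The point rests on what the article does commit to, which is full use of series that it expects to be incomplete.

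**Nothing shows that completion differs by diagnosis.** This stands too. It is tempting to say that diagnosed women will keep answering while healthy controls drift away. The documents do not support that. Controls are women without a diagnosis, not women without symptoms, and the Introduction says the app alerts users whose symptoms suggest endometriosis. Undiagnosed women may have as much reason to continue. The direction and size of any difference are unknown.

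**The count-only AUC overstates the harm.** Correct. A reader might take 0.74 as the inflation. It is the discrimination of the count by itself. Added to a symptom score of 0.75, it raises the AUC by 0.08, and only under strongly unequal retention.

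**The scenario list is open-ended.** The three scenarios are introduced as examples, so it cannot be said that no planned check would reveal the problem, only that none of the named ones would.

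**The 13-form model may not describe the data.** The article speaks of more than a million patient records, while 10,000 women × 13 forms is at most 130,000. Series may include other app entries. The figures are then a rough guide, but the mechanism is unchanged because app entries can also vary with engagement.

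**Conclusion.** The point holds in conditional form. The article commits the LSTM to full use of time series that will be unequal in length, and it fixes no common window. Neither its filter nor its named scenarios equalise or test length. If completion differs by diagnosis, in either direction, apparent discrimination could be too high for new users.

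The size cannot be derived from the documents. Under the assumed retention rates, inflation of an AUC of 0.75 runs from 0.004 to 0.080, and it is zero if completion is equal. The calculation assumes that the model makes the best possible use of the count, so it is an upper figure for count information within each scenario. Gaps and timing, which it leaves out, could add to it.

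This is an inexpensive improvement to the analysis of the primary objective. It is not a demonstrated error in the plan.

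**What to change.** Keep the full-series LSTM and add two reports beside it.

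1. **Completion and a negative control.** Report the number of completed forms by diagnosis group. Report the AUC of a model given only the number and timing of completed forms. A value near 0.5 would support the LSTM result; a clearly higher value would show how much label information completion carries.
2. **Common landmarks.** Report performance at the same points for both groups, for example baseline only, then baseline plus the same first 3 monthly forms. No input should carry later length or gaps.

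The cost is a few sentences of analysis text and a few extra model runs, and reported accuracy may be lower. The landmark results have a limit of their own: every set after baseline contains only women retained to that point. At 95% v 85% monthly retention, the 3-month set would hold 0.95^3 = 86% of cases and 0.85^3 = 61% of controls. The baseline-only result, which involves no such selection on later retention, should therefore always be shown alongside.
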